## Abstract

With changing drug supplies and associated drug consumption behaviors, HIV transmission has increased among people who inject drugs in the United States. HIV testing and referrals to effective prevention and treatment services are critical for individual and population health, yet multilevel barriers limit access to HIV testing for this population, even within syringe services programs (SSPs). In this organizational-level interrupted time series randomized controlled trial, we will assess the effectiveness and cost-effectiveness of an implementation strategy, the Systems Analysis and Improvement Approach (SAIA), in optimizing HIV testing and referrals to appropriate clinical services among U.S. SSPs. From 01/12/2023 to 01/07/2025, we will recruit a diverse sample of 32 SSPs nationally that directly provide HIV testing to participants. SSPs will be randomized to the active implementation arm (i.e., SAIA-SSP-HIV) or an implementation-as-usual arm (n = 16 organizations per arm). SAIA-SSP-HIV is a flexible, data-driven implementation strategy designed to help optimize SSPs’ delivery of HIV testing and referrals to appropriate clinical services for HIV prevention (e.g., pre-exposure prophylaxis) and treatment. In the active implementation arm, trained SAIA specialists will guide SSPs through three cyclical steps over 12 months: (1) process mapping to identify organization-specific needs, (2) cascade analysis and prioritization of areas for improvement, and (3) testing solutions through continuous quality improvement. In both arms, we will collect outcome data over 21 months (3-month lead-in period, 12-month implementation period, 6-month sustainment period). We will assess the initial and sustained effectiveness of SAIA and calculate its cost and cost-effectiveness. This trial presents a novel opportunity to test the effectiveness of an organization-level implementation strategy for optimizing the delivery of HIV screening and referrals in community settings that are frequented by an at-risk population. If successful, SAIA-SSP-HIV could be adapted for other infectious or chronic disease care cascades within SSPs.

**Trial registration:** ClinicalTrials.gov: NCT06025435.

## Introduction

Although HIV prevalence among people who inject drugs (PWID) in the United States dropped dramatically from 40% [1] in the 1990s to 7%–10% by 2018 [2,3], HIV outbreaks associated with injection drug use have increased over the past decade, causing renewed concern about a possible resurgence of HIV in this vulnerable population [4–8]. In the context of the ongoing opioid crisis, several factors may be contributing to this increased risk of HIV transmission among PWID. First, unregulated drug supplies contain rising quantities of fentanyl [9], which increases injection frequency and has been associated with receptive syringe sharing (i.e., using a used syringe after another person has used it) [10–12]. Second, widespread use of psychostimulants such as methamphetamine is likely contributing to increased sexual exposure to HIV [13]. Furthermore, PWID experience multilevel barriers to healthcare, reducing their likelihood of accessing HIV testing and evidence-based prevention and treatment services [14,15], highlighting a need to improve HIV services delivery in alternative, low-barrier settings.

Syringe services programs (SSPs) are a promising venue for increasing access to HIV testing and prevention and treatment services. PWID often prefer accessing health services in community-based SSPs, where staff represent trusted sources of health information and support and can effectively provide infectious disease prevention and treatment services (e.g., HIV and hepatitis C testing and treatment) and medications for opioid use disorder [15–18]. However, while many SSPs came into existence with a goal of addressing HIV among PWID [19], most have adapted to also focus on additional, emerging health crises (e.g., drug-related overdose deaths [20], shifting drug use patterns [21], COVID-19 [22]), likely reducing attention on and resources directed towards HIV services [22–25]. Even for SSPs that have the capacity to provide onsite HIV testing, de-prioritization of HIV among SSPs’ participants and inefficiencies within service delivery may suppress the reach of HIV screening and referrals [25]. To reinvigorate HIV services delivery and engage more PWID in these services, SSPs likely need additional support at the organizational level.

We designed a randomized controlled trial (RCT) to test the effectiveness of an evidence-based implementation strategy, the Systems Analysis and Improvement Approach (SAIA), in increasing SSPs’ provision of HIV testing and referrals to appropriate clinical services, which, depending on HIV test results, could involve prevention or treatment services (e.g., pre-exposure prophylaxis or antiretroviral therapy). SAIA is a flexible, multicomponent implementation strategy that supports frontline service providers by providing a comprehensive view of care delivery cascades, helping to identify areas for improvement, and iteratively testing approaches to improve quality of care [26]. In the context of HIV services, SAIA has been shown to improve the delivery of services for preventing mother-to-child HIV transmission in Mozambique, where it was also deemed acceptable among providers [27]. Recently, members of our research team adapted and pilot tested SAIA for improving the naloxone delivery cascade within SSPs, demonstrating its potential within this nonclinical community setting [28]. However, numerous differences exist between the delivery of HIV services in clinical settings SSPs, and between naloxone and HIV services delivery (e.g., staff capacity, resource and infrastructure availability, relative prioritization, complexity, standardization), warranting a need for additional implementation research on the SAIA strategy for increasing HIV services delivery within SSPs.

We developed SAIA-SSP-HIV to improve HIV services delivery among SSPs across the United States. As there is wide variation in SSPs’ provision of HIV services, and few SSPs can provide clinical services directly onsite, we focus our efforts on increasing HIV testing and the subsequent provision of referrals to appropriate clinical services depending on HIV test results. As SAIA-SSP-HIV moves beyond individual-level interventions to target organizational-level factors that impede or promote the delivery of HIV testing and subsequent referrals, it has the potential to reinvigorate and optimize these services within SSPs, effectively reaching larger numbers of PWID and better promoting individual and population health. This protocol paper describes the rationale and methods for the ongoing SAIA-SSP-HIV implementation trial, which was prospectively registered on September 6, 2023 (ClinicalTrials.gov: NCT06025435).

## Materials and methods

### Aims, objectives, and hypotheses

The overall aim of this study is to assess the impact of SAIA-SSP-HIV on U.S. SSPs’ delivery of HIV testing and referrals to appropriate clinical services, as compared to an implementation-as-usual (IAU) condition. The specific objectives and related hypotheses of this organizational-level interrupted time series randomized controlled implementation trial include:

To test the effectiveness of SAIA-SSP-HIV on improving SSPs’ delivery of HIV testing and referrals to appropriate clinical services (i.e., for HIV prevention or treatment, depending on HIV testing results). We hypothesize that, compared to the IAU arm, SSPs randomized to the SAIA-SSP-HIV arm will demonstrate significantly higher proportions of participants receiving HIV testing and referrals over a 12-month implementation period.To test the sustained effectiveness of SAIA-SSP-HIV on improving SSPs’ delivery of HIV testing and referrals to appropriate clinical services. We hypothesize that, compared to IAU, SSPs randomized to SAIA-SSP-HIV will sustain higher proportions of participants receiving HIV testing and referrals during a 6-month sustainment period (i.e., 6 months after the active treatment phase).To estimate the costs and cost-effectiveness of SAIA-SSP-HIV on improving SSPs’ delivery of HIV testing and referrals to appropriate clinical services. We hypothesize that SAIA-SSP-HIV will be cost-effective at increasing the proportions of participants receiving HIV testing and referrals compared to SSPs randomized to IAU.

### Expected results of the research

To expand SSPs’ reach to underserved populations at elevated HIV risk;To determine the effectiveness of the SAIA implementation strategy in addressing multilevel challenges SSPs face in delivering HIV testing and subsequent referrals; andTo inform the use of the SAIA strategy for optimizing other infectious disease care cascades within SSPs.

### Ethical considerations

The Institutional Review Board of the University of California, San Diego reviewed this protocol and provided a Not Human Subjects Research determination on July 13, 2022 (protocol # 804265).

### Study setting

SSPs are expanding across the United States, with 473 programs listed in the public-facing directory of the North American Syringe Exchange Network as of February 2024 [19]. SSPs offer numerous services to people who use drugs and PWID, including sterile drug consumption supplies (e.g., syringes, other drug use equipment), overdose education and naloxone distribution, and testing for HIV and other infectious diseases (e.g., hepatitis C). Some SSPs also provide case management services, basic clinical services (e.g., vaccinations, wound care), medications for opioid use disorder, and supported referrals to external health and substance use disorder treatment services [29,30]. Three decades of research show that SSPs are safe, cost-saving, and effective in reducing the transmission of HIV and other infectious diseases [29]. Although there is wide variation in the size, scope, service delivery models, and reach of SSPs, most programs offer at least some HIV testing and referral services [30]. However, similar to the healthcare system, the COVID-19 pandemic disrupted routine service delivery for many programs and presented particular challenges to the delivery of services requiring in-person interaction, such as HIV testing and subsequent referrals [30]. Combined with public health authorities’ and funders’ increasing prioritization of overdose prevention, it is unlikely that most SSPs have resumed HIV testing at pre-pandemic levels. Efforts are thus needed to identify and reduce service delivery inefficiencies to optimize HIV testing and referral services [31].

The HIV prevention and treatment cascades begin with targeted outreach efforts to identify and engage at-risk individuals in HIV testing. In the general U.S. population, it is estimated that 15.5% of the approximately 1.1 million people living with HIV/AIDS are unaware their status, which can threaten individual health and enable ongoing transmission [8]. Despite the elevated risk of acquiring HIV through injection and sexual exposures [32], given the low levels of healthcare utilization among PWID, it is unlikely that most PWID receive the annual HIV testing recommended by the U.S. Centers for Disease Control and Prevention [33]. While most SSP participants should be offered HIV testing as part of routine service delivery encounters, the methods and extent to which frontline SSP staff engage participants in HIV testing and referral services varies across organizations [34], and levels of participant uptake of HIV testing may be lower than desired [25].

As of February 2024, 71% of the 473 publicly listed U.S. SSPs were providing HIV testing or education [19]. The most common HIV testing process within SSPs and other nonclinical settings involves conducting an initial HIV test, often through point-of-care “rapid” testing. Due to limitations in staff training and certifications, space, funding, and prioritization, fewer programs utilize onsite laboratory-based testing requiring a blood draw [33,34]. Following HIV testing, most SSPs then refer participants to external organizations, especially those with which they have established relationships, for clinical services including antiretroviral medications for HIV prevention (i.e., pre-exposure prophylaxis) or treatment [30,33,35]. Some SSPs also provide referral supports including transportation, incentives, and “warm hand-offs” or introductions to nearby clinical providers, though it is unknown how consistently programs provide these supports or which supports are most successful in linking participants to clinical services [8]. Rarely, SSPs support participants with later steps in the HIV prevention and treatment cascades, including medication storage and adherence supports, depending on capacity and infrastructure availability [33]. Drop-offs and inefficiencies early in the HIV prevention and treatment cascades (e.g., testing and subsequent provision of referrals) threaten subsequent cascade steps (e.g., accessing evidence-based HIV prevention and treatment services). As such, addressing these drop-offs within SSPs will be critical to meeting the goals of the national Ending the HIV Epidemic initiative [8].

### Implementation strategy

This trial will test the impact of SAIA-SSP-HIV on SSPs’ delivery of HIV testing and subsequent referrals to appropriate clinical services. As an overview, the Systems Analysis and Improvement Approach (SAIA) is a multi-component implementation strategy designed to help organizations optimize their delivery care cascades [26]. Extensive prior work has documented SAIA steps and mapped them to discrete implementation strategies as defined by the Expert Recommendations for Implementing Change [26,36]. Briefly, SAIA is comprised of three overarching steps that may be repeated iteratively. The first step is “cascade analysis” to assess organizations’ performance across sequential outcomes within their service delivery cascades. Typically, these outcomes are summarized over periods of time (e.g., weeks, months) using a Cascade Analysis Tool (CAT) that helps visualize organizations’ care cascades, identify drop-offs and inefficiencies, and determine which steps could have the greatest potential for improvement if specific inefficiencies are addressed. The second step is “process mapping,” which involves a trained SAIA specialist working with organization staff to understand and illustrate the typical flow of participants through service delivery. The third step involves continuous quality improvement (CQI) using data from the CAT to inform which steps of the service delivery process have the most potential for improvement and developing solutions to optimize service delivery at these steps. After the team tries specific, locally identified solutions, the SAIA specialist assists staff in revisiting the CAT to evaluate the impact of the solutions and determine whether to adopt them permanently, adapt and re-evaluate solutions in another cycle, or abandon them altogether. Because SAIA is designed to be responsive to the needs of the organization, management and frontline staff should be engaged in each of these steps through regular SAIA strategy meetings facilitated by the SAIA specialist. Each of SAIA’s three steps have been adapted as follows to focus on these specific outcomes early in the HIV prevention and treatment cascades:

#### 1. The HIV-CAT.

The SAIA specialist will work with up to six SSP staff members, including leadership, management, and frontline (i.e., participant-facing) staff to interpret the HIV-CAT to better understand areas of drop-off related to the delivery of HIV testing and referrals to appropriate clinical services. Organizational needs and preferences, as well as potential magnitudes for improvement (automatically calculated within the HIV-CAT), will inform decisions about which drop-off points are prioritized as areas for optimization.

#### 2. Process mapping.

SAIA specialists will work with staff to discuss and illustrate the flow of SSP participants through HIV services within their SSP. SAIA specialists will work with staff to identify processes believed to contribute to drop-offs and inefficiencies in the cascade, discuss and select potential solutions (i.e., “micro-interventions” like reorganizing the flow of participants through the SSP, incentivizing HIV testing, or scheduling structured staff supervision), and develop plans for implementing solutions based on feasibility and potential cascade gain.

#### 3. Continuous quality improvement.

SSP staff will implement the selected solutions for a minimum of four weeks. Some solutions may take longer than others to implement due to their complexity, the length of time required for observing results, or the resources available within programs (e.g., for hiring staff for a new role compared to displaying a sign that clearly describes when and where HIV testing services are offered). SAIA specialists will convene monthly meetings with SSP staff to help them review the HIV-CAT and evaluate whether the solutions implemented produced the desired improvements. Based on these results, SSP staff may decide to adopt specific solutions permanently, adapt and re-evaluate them in another cycle, or abandon them altogether and test entirely different solutions. By repeating the process of cascade analysis, process mapping, implementation of micro-interventions, and assessment of effects on cascade performance, the SAIA specialist will guide the SSP through multiple rounds of CQI over the 12-month implementation period.

### Implementation strategy fidelity and specification

A core outcome of implementation research involves intervention fidelity, or “the extent to which an intervention is delivered as intended [37].” As a potential moderating variable in intervention research, fidelity measurement is needed to reduce the risk of a Type III error (i.e., ensuring the treatment was delivered as intended and is therefore responsible for any change in outcomes). Given that implementation strategies often represent complex behavior change efforts themselves (e.g., SAIA specialists’ meetings with SSP staff), assessing fidelity of implementation strategies is similarly and critically important in trials of implementation strategies like SAIA-SSP-HIV. In addition to implementation strategy fidelity assessment, strategy specification facilitates an understanding of what strategy activities entailed, ultimately improving replicability in subsequent research or practice settings. Implementation strategy specification should delineate the actor, action, action target, temporality, dose, implementation outcome affected, and justification [38]. For this trial, we build upon Akiba et al.’s adapted specification of SAIA, which expanded the Proctor et al. specification components to include additional components focused on implementation strategy fidelity like meeting frequency, consideration of content covered in specialist sessions, session duration, quality of interactions, and participant responsiveness (Table 1) [39]. Implementation outcomes are described in greater detail below.

**Table 1 pone.0319340.t001:** SAIA-SSP-HIV implementation strategy specification and fidelity.

Name it:	Systems Analysis and Improvement Approach for HIV (SAIA-SSP-HIV)
**Define it:**	Facilitate development of a quality monitoring system to conduct cyclical small tests of change led by the organizational implementation teams.
**Specify it:**	
**Actor**	External specialist works and facilitates discussion with the organization’s implementation team with regards to the SAIA-SSP-HIV process.
**Actions**	Identify gaps: Present data evaluating the SSP’s^a^ delivery of the HIV care cascade with HIV-CAT.^b^ Facilitate discussions and support the implementation team to identify and develop consensus with regards to the areas of attrition along the HIV care cascade that they would like to address. Identify causes and opportunities: a. Facilitate discussions with the implementation team to review the SSP’s service structure and draw process maps documenting the flow of participants through the HIV care cascade to understand (i) why there are drop-offs or inequities in distribution at different points (root causes of participant attrition) and (ii) what it would take to address those issues (opportunities to streamline workflows and address key points of attrition). b. Assist team in developing consensus about programmatic modifications based on their importance and feasibility. Conduct CQI:^c^ a. Support and mentor the implementation team in operationalizing programmatic modifications. b. Present follow-up data on the delivery of the HIV care cascade for the implementation team to assess changes resulting from programmatic modifications. c. Repeat above actions after conclusion of the cycle.
**Action target**	Leverage programmatic data to facilitate CQI and foster a learning climate.
**Temporality**	After training the implementation team on the SAIA process and integrating enhanced instruments to collect program data into workflows to track HIV care cascade delivery indicators.
**Fidelity**	Content: Specialist completes actions 1–3 with SSPs. Coverage: SSP staff are present during actions 1–3. Duration: Actions 1, 2, and 3 take ~ 60min each. Frequency: Specialist visits SSPs in person during months 1, 4, 7, and 10. Specialist meets SSPs virtually during all other months in active phase. Quality: Specialist forms rapport with SSP staff, flexibly attends to their unique needs, and motivates SSP staff to engaged with actions 1–3. Participant responsiveness: SSP staff like working with the specialist and like participating in actions 1–3.
**Targeted implementation outcomes**	Implementation effectiveness relative to IAU.^d^ Reach: Number of HIV tests conducted Fidelity (to delivery of the HIV care cascade): Number of referrals to appropriate clinical services for HIV prevention and treatment
**Justification**	SAIA-SSP-HIV combines a broad view of the service system with iterative improvement cycles in a user-friendly way; by leveraging SAIA-SSP-HIV, SSPs can identify fillable gaps in the delivery of the HIV care cascade and apply locally generated solutions that have a higher likelihood of leading to measurable and sustained improvements in fidelity to the cascade and penetration of HIV services.

^a^SSPs, syringe services programs; ^b^HIV-CAT, HIV cascade analysis tool; ^c^CQI, continuous quality improvement; ^d^IAU, implementation as usual. Table adapted, with permission, from Akiba et al. [39].

### Study design

To meet our specific objectives, we will conduct a parallel-group interrupted time series RCT with 32 U.S. SSPs randomized to receive SAIA-SSP-HIV or IAU for 12 months (n = 16 organizations per arm; Fig 1). SSPs randomized to the IAU arm will not receive the active SAIA strategy or any support from SAIA specialists (i.e., IAU is characterized by the absence of SAIA-SSP-HIV).

**Fig 1 pone.0319340.g001:**
[figure not shown]
Schedule of enrolment, interventions, and assessments for the SAIA-SSP-HIV trial.

### Recruitment and pre-randomization procedures

We will recruit SSPs from 01/12/2023 to 01/07/2025. Organizations will be considered eligible for the trial if they meet the following inclusion criteria: (1) located in a U.S. state, territory, or tribal nation, (2) operate a dedicated SSP that provides access to sterile syringes and injection equipment, and (3) have directly provided their own (i.e., not through referrals to external organizations) HIV testing services to participants within the past 30 days. SSPs will be excluded if they (1) are participating or have participated in other studies involving SAIA or its key components, or (2) intend to stop providing HIV testing services to participants within the next 21 months.

Initial recruitment efforts will be targeted towards SSPs known to our national investigator team through previous research. From there, we will leverage publicly available SSP organizational directories (e.g., the North American Syringe Exchange Network [NASEN]). Study coordinators will first email identified SSPs’ directors (e.g., executive director, chief executive officer) to briefly describe the study and request an introductory call to provide greater detail on study procedures. For SSPs expressing interest in enrolling in the study, the coordinator will set up an enrollment appointment using Zoom’s web-enabled audio and screen-sharing technology and assign a unique identification code. Recruitment will occur over 15 months, targeting two to three enrollments per month. If an SSP declines or fails to respond after three contact attempts, we will replace the organization with another potentially eligible SSP.

Following enrollment, SSPs will enter a three-month lead-in period beginning on the first day of the month they are enrolled in. During lead-in, SSPs will be asked to submit data on outcomes (HIV testing and referrals) for the month prior, disaggregated by week. Outcome data, described in greater detail below*,* will include total numbers of SSP participant encounters, HIV tests conducted, and referrals to appropriate clinical services. Outcome data will be collected using an online survey distributed automatically through REDCap, a secure online platform for managing research project surveys. Study coordinators will provide technical support to SSPs as needed to ensure timely and complete outcome data submissions.

One to two weeks prior to the end of the three-month lead-in period, we will ask organizational directors from enrolled SSPs to complete an interviewer-administered baseline survey, lasting 45–60 minutes (conducted on Zoom with the interviewer entering data into REDCap). Baseline surveys will assess programs’ internal and external characteristics, [40] implementation climate, HIV services, and operational costs.

At the end of the lead-in period, SSPs will be randomly assigned to receive SAIA-SSP-HIV or IAU using REDCap’s online randomization module. As our formative research suggests that SSPs’ HIV services delivery models vary significantly depending on organization type (i.e., non-governmental community-based organization [CBO] vs. local or regional health department or clinic), randomization will be stratified into two groups. Study coordinators will conduct randomization and deliver results to primary SSP contacts over Zoom after administering the baseline survey.

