### Data collection activities

#### Implementation determinants and context variables.

Previous implementation studies, including those utilizing SAIA, have demonstrated the importance of external context, implementation climate, and leadership engagement as determinants that influence and are influenced by quality improvement approaches [28,41]. During the initial baseline survey conducted prior to randomization, we will assess all enrolled SSPs’ basic organizational characteristics (e.g., funding sources, staff size, budget), implementation climate, and leadership engagement, which are implementation determinants we have observed in our preliminary research with SSPs [28,42]. We will measure implementation climate and leadership engagement again at 12-month follow-up for all enrolled SSPs, and once more for the SAIA-SSP-HIV arm only at 18 months, marking the end of the sustainment period.

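### Under the stated reporting lag, the third lead-in month's counts would ordinarily be self-reported after the SSP knows its arm, and nothing stated requires them before allocation is released

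*Protocol article*

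**What the plan says.** All timing statements below are in the protocol article, mostly under Recruitment and pre-randomization procedures.

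- Start and length of lead-in: "Following enrollment, SSPs will enter a three-month lead-in period beginning on the first day of the month they are enrolled in".
- Reporting lag: "During lead-in, SSPs will be asked to submit data on outcomes (HIV testing and referrals) for the month prior, disaggregated by week".
- Baseline survey: "One to two weeks prior to the end of the three-month lead-in period, we will ask organizational directors" to complete it.
- Randomization: "At the end of the lead-in period, SSPs will be randomly assigned to receive SAIA-SSP-HIV or IAU". Data management repeats this timing.
- Disclosure: "Study coordinators will conduct randomization and deliver results to primary SSP contacts over Zoom after administering the baseline survey". No date or interval is given.
- Order of survey and allocation, under Implementation determinants and context variables: "During the initial baseline survey conducted prior to randomization".

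Other parts bear on the point. Under Primary outcome variables, the counts are submitted by the SSPs themselves on monthly REDCap forms. Analyses and power calculations mentions single blinding for the statistical analyses only. Under SAIA-SSP-HIV specialist activities, specialists meet SAIA sites twice a month for the first three months and use the initial visits partly to look at how data are documented and collected. Table 1 puts an in-person visit in month 1. Under Study design, IAU sites receive no specialist support.

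**The concern.** The lead-in is the pre-intervention segment of the interrupted time series, and it is meant to be the same kind of measurement in both arms. That holds only if its counts are fixed before anyone supplying them knows the allocation. With a one-month lag and randomization at the end of lead-in, the last baseline month is compiled by staff who know their arm.

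There is also a one-sided route to differential recording that needs no bad faith. In the month when the month-3 form would be filled in, SAIA sites may be going through a specialist review of their documentation, and IAU sites are not. If that makes SAIA sites count more completely, or differently, the change reaches their last baseline weeks but not those of the control arm.

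These weeks sit next to the interruption. The model expects a flat lead-in and compares later change by arm, so an arm-dependent error here could disturb both the baseline level and the lead-in slope. The direction is unknown: it could inflate the estimated effect or mask it.

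**Working it through.** **The plan's own figures.** The follow-up structure reproduces: 3 + 12 + 6 = 21 months. The target shift reproduces: 0.8 × 2.94 = 2.352, stated as 2.35. The target slope reproduces: 2.352 / 11 = 0.214, stated as 0.21 per week. The stated power comes from a simulation whose pilot random effects are not given. It does not bear on this point.

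**Calendar of forms.** Lead-in months 1, 2 and 3 start on the first of a month, and each form covers the preceding month:

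- Form sent in lead-in month 1: the month before lead-in.
- Form sent in lead-in month 2: lead-in month 1.
- Form sent in lead-in month 3: lead-in month 2.
- Form sent in month 4, which is implementation month 1: lead-in month 3.

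Randomization is at the end of lead-in month 3. Unless it is held back for the last form, that form is completed after disclosure. The article states no such hold and gives no due date for the form.

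**Share of lead-in reported after disclosure** (taking three months as about 13 weeks):

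- By months: 1/3 = 33%.
- By weeks: 4/13 = 31% to 5/13 = 38%.
- As a share of the whole series: 1/21 = 4.8%.

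**Share of lead-in services delivered after disclosure:**

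- Result given at the end of lead-in, as stated: 0%.
- Result given on the survey call: 1/13 = 8% to 2/13 = 15%.

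**Illustration of size.** The document gives no rate of differential recording, so the percentages here are assumptions. The inputs are the run-in mean of 7.32 people tested, taken as a weekly figure because the simulation uses weekly assessments, and an error confined to the last 4 of 13 weeks in one arm.

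- Shift in that arm's lead-in mean = p × 7.32 × 4/13.
- Shift in a simple least-squares lead-in slope = p × 7.32 × 18/182. With weeks 1–13 centred at 7, the last four deviations sum to 3 + 4 + 5 + 6 = 18, and the squared deviations sum to 182.

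| Assumed p | Shift in mean (per week) | Share of 2.35 | Shift in slope (per week) |
|---|---|---|---|
| 5% | 0.11 | 5% | 0.04 |
| 10% | 0.23 | 10% | 0.07 |
| 20% | 0.45 | 19% | 0.14 |

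These are shifts in the lead-in data. How much of a shift would carry into the treatment-effect estimate depends on the fitted growth model and is not derived here.

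**The case against.** The strongest reply is that the article never says the month-3 form comes in after disclosure. It gives a lag but no deadline, and nothing rules out holding the randomization call until that form has arrived. Form sequencing is an operational detail that an article may leave to the full protocol, and the schedule figure is not available here. This stands in part: late reporting is an inference from the stated rules. But the article does fix the lag, the survey window, the randomization point and the mode of disclosure. Followed as written, these put the last form after disclosure, so the point does not rest on silence alone.

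A reader might infer three stronger claims, and the document supports none of them.

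- That a third of baseline activity takes place with the arm known. It does not: under the stated timing, month-3 services are delivered before allocation, and only the compiling of counts can fall later.
- That allocation is in fact disclosed one to two weeks early. That requires the survey and the result to share one call, which is at odds with randomization at the end of lead-in, stated twice. The disclosure sentence can be read as fixing only an order. The wording leaves the early reading open and should be tidied, but it does not establish it.
- That the bias is a known fraction of the target effect. Any such fraction restates an assumed misreporting rate.

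It is also fair that the trial has a concurrent randomized control arm, so the comparison does not rest on the lead-in alone. The 18 later months are in any case self-reported by programs that know their arm. Both facts limit the harm. Neither is a reason to let the same exposure into the baseline, the one segment where it can be avoided.

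**Conclusion.** The point holds as a weakness in sequencing, of minor to moderate severity. Under the reporting lag and the stated randomization time, about a third of the lead-in series (33% by months, 31–38% by weeks) would ordinarily be self-reported after the SSP has been told its arm. In SAIA sites this may coincide with the specialist's documentation review. No stated rule requires that form first.

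The conclusion assumes that the month-3 form follows the same lag as the others and that randomization is not held for it. The exposure is to differential recording of past activity. Exposure of service delivery is 0% as stated, and would be 8–15% of lead-in weeks only on the survey-call reading. The resulting bias cannot be sized from the document. The 0.23 tests per week figure is an illustration under an assumed 10% differential. Separately, the disclosure sentence and the end-of-lead-in statement should be reconciled so that only one reading is possible.

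**What to change.** 1. Require each SSP to submit, and the study to lock, all lead-in weekly counts, including month 3, before the REDCap randomization module is opened for that SSP.
2. State that the result is given only after lead-in ends and not on the baseline survey call.
3. Record form-submission and disclosure dates for every SSP. The trial is described as ongoing, so for any site already randomized, run a sensitivity analysis that drops lead-in weeks reported after disclosure.

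The cost is a delay of days to about two weeks between the end of lead-in and the start of SAIA, and a separate short call where a site would otherwise have combined the two. Because forms are monthly and lead-in starts on the first of a month, the delay creates some weeks that are neither lead-in nor implementation, or moves the start of implementation to mid-month. The protocol should say how those weeks are labelled and apply the same rule in both arms, so that the 3 + 12 + 6 month structure stays comparable. No new outcome items are needed.
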